## Abstract

**Background:**

Knee osteoarthritis (KOA) is one of the most common bone and joint diseases. As one of the main non-drug therapies, acupuncture is widely used to treat KOA, although the evidence for its efficacy is inconclusive. The objective of this pilot trial is to clarify the clinical efficacy and safety of fire acupuncture in the treatment of mild to moderate KOA and to provide high-quality data for further research.

**Methods/design:**

This study is a prospective randomized controlled pilot trial in which 120 patients with mild to moderate KOA will be randomly allocated in equal proportions to a fire acupuncture group or a general acupuncture group. They will receive acupuncture for six sessions over 2 weeks. The primary end point is success rate, which will be calculated based on the change from baseline of the pain and function scores in the Western Ontario and McMaster Universities Osteoarthritis Index at 4 weeks. Secondary end points include the proportion of patients achieving clinical improvement based on: (1) the OMERACT-OARSI responder criteria, (2) levels of matrix metalloproteinase 3, interleukin 1β, and tumor necrosis factor α in blood, and (3) a subjective efficacy evaluation from patients.

**Trial registration:**

Chinese Clinical Trial Registry, ChiCTR1800019162. Registered on 29 October 2018.

## Background

Knee osteoarthritis (KOA) is one of the most common musculoskeletal disorders [1]. Its prevalence rate is 49% among people over 60 and 80% among people over 75 in China. One third of people over 65 suffer from KOA, according to epidemiological surveys [2]. Worldwide, an estimated 25,000 people suffer from KOA [3]. Most have radiological or clinical evidence of osteoarthritis [4], and the incidence of the disease has been increasing with the aging of the population [5]. Its high incidence and high disability rate not only bring a heavy economic burden to patients, but also seriously affect their quality of life [6]. If symptoms persist, patients may have low levels of social activity and abnormal psychological functioning, which may eventually lead to a decline in the quality of life and even an inability to live independently, causing heavy psychological pressure and a burden on the patient and their family.

Analgesics—such as non-steroidal anti-inflammatory drugs, opioids, and non-opioid central analgesics (such as tramadol)—are still recommended to treat the disease, according to the guidelines for the diagnosis and treatment of KOA published by the American Academy of Orthopaedic Surgeons in 2013 [7] and those published by the National Institute for Health and Care Excellence in 2014 [8]. However, drug treatments can cause serious gastrointestinal complications, such as ulcers, perforations, and bleeding, and the risk increases with age and treatment duration. At present, the treatment for KOA is pain relief, symptomatic treatment, maintenance, or improvement of joint function, since there is no effective way to completely block or reverse the development of KOA. Most patients with advanced KOA have to “cure” it by undergoing knee replacement. Unfortunately, many KOA patients are unable to undergo a knee replacement due to their physical condition or affordability. Therefore, a safe and effective therapy for KOA that is free of side effects is urgently required to improve patients’ quality of life and reduce the national medical burden.

Acupuncture is important in traditional Chinese medicine as a non-drug therapy. It has been used for more than 2000 years in China [9]. In fire acupuncture (FA), a heated needle is inserted into an acupuncture point to eliminate the symptoms of a disease [10]. A meta-analysis published in *Evidence-Based Complementary and Alternative Medicine* showed that FA has a higher response rate and higher cure rate in the treatment of KOA [11].

Although FA is widely used to treat KOA and has achieved good results, there is still a lack of good medical evidence to verify whether it is beneficial. In addition, the molecular biological mechanism is still unclear. Fire needle therapy has been developed over thousands of years. It has a wide range of clinical applications in China, with a definite curative effect and a wide range of indications. Studies have shown that FA can reduce the level of some inflammatory cytokines that are elevated in KOA, such as interleukin 1 (IL-1), interleukin 6 (IL-6), and tumor necrosis factor α (TNF-α) [12].

Nevertheless, none of the 13 studies included in the meta-analysis in *Evidence-Based Complementary and Alternative Medicine* [11] were of sufficient quality. Most of the research into FA quoted in the literature is of poor quality, for example, the randomization methodology is often unclear and there can be issues with the selection of the control group. Thus, doctors and patients may have concerns about the efficacy and safety of FA. Therefore, high-quality prospective randomized controlled trials are needed to determine the clinical efficacy and safety of FA in treating mild and moderate KOA and to explore the mechanisms of action.

## Methods/design

### Study design

The study is a prospective multi-center parallel randomized controlled trial. We will enroll patients from Beijing Hospital of Traditional Chinese Medicine (Capital Medical University) and Beijing Huairou District Hospital of Traditional Chinese Medicine with mild to moderate KOA, according to the inclusion and exclusion criteria, from January 2019 to December 2019. Participants will be randomly allocated to one of two groups and will receive treatment for 2 weeks. The trial has been registered with the Chinese Clinical Trial Registry (ChiCTR1800019162). All items from the World Health Organization’s trial registration data set have been entered into the registry. The intervention includes six sessions of acupuncture and two follow-up visits (Fig. 1 and Table 1).

**Fig. 1 Fig1:**
[figure not shown]
Trial flow chart. KOA, knee osteoarthritis

**Table 1 Tab1:** Schedule of enrollment, interventions, and assessments

	Baseline	Treatment phase	Follow-up phase	
	−1 day	0 day	2 weeks	4 weeks
Patients				
Informed consent	×			
Sign informed consent		×		
Medical history	×			
Physical examination	×			
Randomization		×		
Intervention FA group (*n* = 60)	Six sessions of FA			
Comparisons GA group (*n* = 60)	Six sessions of GA			
Outcomes				
WOMAC		×	×	×
OMERACT–OARSI		×	×	×
MMP-3		×	×	
IL-1β		×	×	
TNF-α		×	×	
SEE		×	×	×
Participant safety				
Adverse events		×	×	×

*FA* fire acupuncture, *GA* general acupuncture, *IL* interleukin, *MMP-3* matrix metalloproteinase 3, *SEE* subjective efficacy evaluation, *TNF-α* tumor necrosis factor α, *WOMAC* Western Ontario and McMaster Universities Osteoarthritis Index

### Inclusion criteria

To be eligible, patients must meet all of the following inclusion criteria:

Aged 38–85 years (either sex)

Meet the diagnostic criteria for primary KOA

Mild to moderate KOA (Kellgren–Lawrence score 1–2)

Able to receive FA treatment

Voluntary participation in the study

Able and willing to sign the informed consent form

### Exclusion criteria

To be eligible, patients must not meet any of the following inclusion criteria:
Secondary KOAThe knee joint has a history of trauma or surgery in the past yearSevere joint deformity (varus or valgus ≥8°)Injection of glucocorticoid into the articular cavity of the target knee within 3 monthsInjection of sodium hyaluronate into the articular cavity of the target knee within 2 weeksHave received acupuncture or moxibustion for symptomatic hip arthritis or patellar arthritis on the same side of the target knee joint within 2 weeksSymptomatic hip or patellar arthritis on the same side of the target knee jointInflammatory or other rheumatic diseaseAcute knee meniscus injuryAcute knee injury or fracture around the kneeTumor around the kneeTuberculosis or idiopathic osteonecrosisTaking paracetamol, non-steroidal anti-inflammatory drugs, or analgesics for other diseasesUncontrolled hypertension or diabetesSevere cardiovascular, pulmonary, liver, spleen, kidney, or hematopoietic diseaseTumor hemorrhagesMental illnessScar diathesis or skin sensory impairmentPregnant or lactating women

### Randomization and allocation concealment

Random permuted blocks will be used. The allocation to the FA group and to the general acupuncture (GA) group will be in a 1:1 ratio. Opaque numbered envelopes will be used to conceal the allocation. Researchers will open the envelopes according to the order of enrollment. The acupuncturists will not be involved in the randomization. Data collectors, data evaluators, and statisticians will be blinded to group assignment. Participants will not be blinded.

### Interventions

This study conforms to the CONSORT [13] and STRICTA [14] criteria. All acupuncturists are required to have had Chinese medical practitioner licenses for at least 20 years and they will receive the same training under the clinical treatment program prior to the study.

The acupuncture sessions will be for 30 min. There will be three sessions per week for 2 weeks, giving six sessions in total. Sterilized medium and coarse He’s fire needles will be used for the FA group. Disposable, sterile steel, 0.30 × 50 mm acupuncture needles (Ande disposable acupuncture needles, Guizhou Medical Co., Guizhou, China) will be used for the GA group. If participants experience pain of intensity ≥ 4 on a 10 cm visual analog scale [15], they will be given Celebrex. Adverse reactions during treatment will be recorded in the case report form.

Patients in both groups will receive basic health management. Blood tests will be performed on day 0 and the second week after the six acupuncture sessions. In this study, we strengthened patients’ self-management by giving them a detailed manual on managing KOA. The manual was developed by the research team based on the second edition of the evidence-based medical guidelines for KOA published by the American Academy of Orthopaedic Surgeons. The manual explains the natural course of the disease, gives advice on how to avoid psychological effects, and describes the drugs used and their side effects. The manual recommends that they (1) maintain good posture, (2) avoid being stationary for a long time, (3) do not run or jump, and (4) minimize their use of stairs, etc. The contents of the manual are explained to the patient in detail before randomization. Subjects were asked to comply with these self-management recommendations for at least 4 weeks after being randomized. Patients with severe pain may take non-steroidal anti-inflammatory drugs, including topical drugs and systemic drugs. They are asked to record the drug used, the frequency of administration, the dosage, and any adverse drug reactions in the manual.

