### Ethics and dissemination

#### Patient consent and dissemination policy

This protocol has been registered with the Chinese Clinical Trial Registry. All participants will be given ample time to consider whether to participate in the study and to sign the informed consent, which includes consent for blood tests. All blood samples taken from participants will be destroyed after the trial. Participants can withdraw their informed consent at any time during the study. We will publish the results of the trial in a peer-reviewed clinical journal for wide dissemination. Participants who experience severe adverse reactions or irreversible injuries as a result of the trial will be reasonably compensated, according to the circumstances.

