### Strengths

In principle, FA has been recognized in China as a relatively safe non-drug treatment. This study will provide further high-quality clinical evidence on the safety of FA. The planned study has the potential to demonstrate that FA is a novel, practical, and effective treatment for KOA. If FA is effective in alleviating pain and improving joint function in patients with KOA, then it could be adopted as a cheap non-drug therapy instead of potentially addictive drugs or surgery, which may help in reducing the living and economic burden on patients. Since FA is simple, fast, cheap, and easy to implement, then if its efficacy and safety in treating KOA are recognized, doctors will have more treatment options for KOA.

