### Limitations

Acupuncturists and participants will not be blinded due to the nature of the intervention. Participants can not be blinded to the study design due to the feeling of the skin during treatment. The acupuncturists will not be involved in assessing outcomes or the data analysis.

Although the duration of treatment for each participant is only 4 weeks, it is possible to compare the efficacy and short-term effect of FA and GA. Due to the short observation time, however, it will not be possible to determine the long-term efficacy of using fire needles. Levels of the inflammatory factors in peripheral blood may increase during the follow-up period rather than decrease as we expect.

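### The rule for recording harms in the case report form is narrower than Table 1 in definition and window, and the short-observation caveat leaves out safety

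*Protocol article*

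**What the plan says.** The Abstract gives safety as an objective beside efficacy. Four places bear on how harms are collected and what will be claimed about them.

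- **Interventions:** "Adverse reactions during treatment will be recorded in the case report form". This is the only sentence in the running text on entering harms in the case report form. The same section gives the schedule: "There will be three sessions per week for 2 weeks, giving six sessions in total".
- **Table 1:** a row headed "Adverse events", marked at day 0, week 2 and week 4.
- **Strengths:** "This study will provide further high-quality clinical evidence on the safety of FA".
- **Limitations:** because observation is short, "it will not be possible to determine the long-term efficacy of using fire needles". Late safety is not mentioned. The same paragraph opens: "Although the duration of treatment for each participant is only 4 weeks".

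Study design describes the course as follows: "The intervention includes six sessions of acupuncture and two follow-up visits". The Abstract, Study design, Interventions and Discussion sections all give 2 weeks of treatment.

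**The concern.** An adverse reaction is an event that someone has already attributed to treatment. An adverse event needs no such judgement. A site that works from the Interventions sentence and a site that works from Table 1 could therefore collect different safety data, both in what counts and in how long it is looked for. There are two sites, and neither arm's acupuncturists or participants are blinded, so a definition that depends on attribution is the weaker basis for comparing arms.

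The arms also differ in what is done to the skin. Fire acupuncture uses 6 or 7 points (five local, one or two pain points), three heated piercings per point, over six sessions: 6 × 3 × 6 = 108 to 7 × 3 × 6 = 126 piercings per patient. A record that dropped unattributed or post-treatment events would weaken the comparison on an objective the trial sets itself. A reader of the Strengths section would not learn that the safety evidence stops at week 4.

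**Working it through.** The document gives no figure to reproduce here. The check sets the passages side by side.

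**Step 1: definition.** Interventions covers reactions attributed to treatment. Table 1 covers events, with no condition on cause.

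**Step 2: window.** Interventions ties recording to the treatment period, and Table 1 runs to week 4.

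- Sessions: 3 per week × 2 weeks = 6, which agrees with the stated total. On this reading treatment ends at week 2, and Table 1 goes on for 4 − 2 = 2 further weeks.
- If the 4 weeks in Limitations is taken as the treatment period, the difference is 4 − 4 = 0 weeks.

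The gap in the window is therefore 2 weeks or none, depending on which statement of duration a reader uses. The gap in definition remains either way.

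**Step 3: what each source covers, with treatment ending at week 2.**

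| Event | Interventions sentence | Table 1 |
|---|---|---|
| Attributed to treatment, by week 2 | covered | covered |
| Not attributed, by week 2 | not mentioned | covered |
| Attributed to treatment, weeks 2 to 4 | not mentioned | covered |
| Not attributed, weeks 2 to 4 | not mentioned | covered |

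The two sources agree on one of the four classes. In the other three the sentence is silent; it does not exclude them.

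**Step 4: the safety claim.** The last scheduled assessment is at week 4, for efficacy and safety alike. Limitations draws the consequence for efficacy only, and Strengths sets no time limit on safety.

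The planned arm size also limits the claim. Assume all 60 fire acupuncture patients are observed to week 4:

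- If no event of a given type is seen, the one-sided 95% upper limit for its true rate is 1 − 0.05^(1/60) = 0.0487, or 4.9%. The two-sided 95% upper limit is 1 − 0.025^(1/60) = 0.0596, or 6.0%.
- The chance of seeing at least one case is 1 − 0.99^60 = 45% at a true rate of 1%, 1 − 0.98^60 = 70% at 2%, and 1 − 0.95^60 = 95% at 5%.

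These figures follow from n = 60. They do not measure the recording conflict, and aligning the wording would not change them. They show only how far a short-term safety statement from this trial can reach.

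**The case against.** The strongest reply is that the two sources can both hold. The Interventions sentence says what is recorded during treatment and does not say that recording stops there. Table 1 covers the whole trial and has a week-4 mark. Since Limitations calls the treatment period 4 weeks, the phrase in Interventions may loosely mean the whole observation period. This reply stands in part: the document does not show that post-treatment events go unrecorded. It does not remove the difference between reactions and events, and it relies on a duration that the rest of the article contradicts.

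A reader might infer more than the documents support:

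- **That half of the observation period yields no safety record.** The week-4 mark in Table 1 contradicts this.
- **That unblinded treating staff filter the events, in favour of fire acupuncture.** No passage says who judges a reaction. The randomization section blinds data collectors and evaluators, and Limitations keeps acupuncturists out of outcome assessment. No direction of bias can be derived.
- **That late skin harm foreseen by the trial is missed.** Scar-prone patients and those with impaired skin sensation are excluded, and the consent section states "Participants who experience severe adverse reactions or irreversible injuries as a result of the trial will be reasonably compensated". This shows that skin risk and lasting injury were considered, but neither passage says that harm appears late. Skin events visible by week 4 fall within Table 1, and no time course is given from which to estimate a missed share.
- **That follow-up of unresolved events, or a symptom checklist, is absent from the trial.** An article may leave such details to the full protocol or the case report form.

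The safety claim has some restraint around it too. The Abstract calls the study a pilot, and Limitations admits the short observation. That admission is attached to efficacy alone.

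**Conclusion.** The point holds as an inconsistency of low severity. The Interventions sentence and Table 1 disagree on definition, and they disagree on window by 2 weeks if treatment ends at week 2. Limitations gives a treatment duration that conflicts with four other sections and blurs the window further. Read literally, the Interventions sentence could let unattributed events and events after the last session go unrecorded. Whether that happens depends on which text the sites follow, and the article does not say. The size and direction of any effect on the comparison between arms cannot be derived.

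The unqualified safety statement in Strengths goes further than observation to week 4 in about 60 exposed patients can support. This rests on Table 1 being the full visit schedule, with nothing planned after week 4, and on the planned 60 patients per arm.

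**What to change.** 1. In Interventions, reword the recording sentence to match Table 1: all adverse events in both arms, whatever their judged cause, entered in the case report form from the first session to week 4, with causality as a separate field.
2. Reconcile the treatment duration in Limitations with the Abstract, Study design, Interventions and Discussion, so that any reference to the treatment period has one meaning.
3. In Limitations, extend the short-observation caveat to safety. In Strengths, limit the claim to short-term safety up to week 4 in about 60 fire acupuncture patients.

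If the case report form already collects all events at week 4, the first change corrects only the text. Otherwise it costs slightly more recording at visits that already take place. The third change makes the safety claim more modest. No visit, treatment or sample size changes.

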### FA group

Acupuncture points are selected based on the *bi* syndrome in traditional Chinese medicine. There are five local points (ST34, ST35, SP10, EX-LE4, and GB34) and one or two pain points (*ashi* points) (Fig. 2). The procedure is as follows:
Place the patient in a supine position with their knees bent.Disinfect the acupuncture points.Heat the tip and middle of the acupuncture needle until it glows redPierce each point three times to a depth of about 0.5 cm, moving the needle quickly in and out. The needle will be heated before each insertion.Press the acupuncture eyes for a moment with a sterile dry cotton ball.

**Fig. 2 Fig2:**
[figure not shown]
Acupuncture points for both groups

### GA group

2The acupuncture points used are the same as those for the FA group. The procedure is as follows:
Place the patient in a supine position with their knees bent.Disinfect the acupuncture points.Insert a needle into each point to the optimum depth. The needles remain in place for approximately 30 min.Remove all needles and use sterile cotton balls to avoid bleeding.

Acupuncturists are instructed to achieve *de qi* and to stimulate the needles manually for at least 10 s.

### Secondary outcomes

The proportion of patients with a clinical improvement: The OMERACT-OARSI responder criteria will be used at weeks 2 and 4 to assess whether a patient has a clinical improvement, and compare whether there is a difference in improvement between the two groups (Fig. 3).Subjective efficacy evaluation: At weeks 2 and 4, a research assistant will ask each patient about the effects of the therapy they received on their KOA compared to the baseline. The evaluation is scored as follows: greatly aggravated –3, moderately aggravated −2, mildly aggravated −1, totally unhelpful 0, very little help 1, moderate assistance 2, and great help 3.Laboratory indicators: Patients’ peripheral blood will be collected at weeks 0 and 2, and levels of matrix metalloproteinase 3 (MMP-3), IL-1β, and TNF-α will be measured by an enzyme-linked immunosorbent assay.

**Fig. 3 Fig3:**
[figure not shown]
OMERACT–OARSI responder criteria

### Sample size

Since no previous multicenter randomized controlled trials have studied the efficacy of FA in treating KOA, this study will provide effect size data for sample size calculations in subsequent large-scale randomized controlled trials. Overall, 120 outpatients and inpatients will be recruited at the two research centers, giving 60 participants per group.

An effectiveness analysis will be conducted using the randomized populations. Participants who have not received any treatment and participants who have received treatment but for whom there is no valid evaluation data will be considered as missing and will be included in the effectiveness analysis.Participants who cannot tolerate treatment after the start of observation, have serious side effects, have less than 2 weeks of treatment, or are lost to follow-up will be considered as cases of shedding. When the participant falls off, the investigator should make an appointment for follow-up, telephone or letter to contact the participant as much as possible, ask the reason, and record the last treatment time to complete the evaluation project. For trial cases withdrawn due to adverse reactions and ineffective treatment, the investigator should take corresponding treatment measures according to the actual situation of the subject. The investigator should indicate the main reason for terminating the trial. If the exfoliation rate exceeds 20% of the total number of participants, the study will be considered a failure and terminated.

